**Discussion:**

This is a multicenter randomized controlled trial for IBS in China. It may clarify the efficacy of acupuncture as an alternative therapy for IBS. This is the first time ever that the potential mechanism of IBS based on genomics has been investigated.

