Despite these findings and advances in IBS research, the pathophysiology of IBS is still poorly understood with no definitive biomarker, thereby hampering the development of effective therapies for IBS [13]. Currently available treatments for IBS can be broadly classified into pharmacological therapies and other interventions, such as dietary and lifestyle modifications [6, 14]. There are various pharmacological treatments for IBS, including 5-HT-receptor modulating agents, antispasmodics, probiotics, and antidiarrheal agents [15]. While some have been found to be effective, they are not uniformly effective across all patients. There are also potential risks of adverse effects and substantial financial burden associated with the use of pharmacological treatments [6, 16].

As a result of dissatisfaction with the effectiveness, safety, and costs of pharmacological treatments, there has been a rise in the use of non-pharmacological therapies, including acupuncture [17]. Acupuncture is an important modality of traditional Chinese medicine (TCM), which involves an insertion of a needle into the body at specific points to prevent and treat various diseases. It has a long history originating in ancient China and has been used for thousands of years to treat digestive problems. In recent research, there has been a growing interest in investigating the possible role of acupuncture in improving symptoms and quality of life in IBS patients [18]. Current evidence suggests that acupuncture is more effective than pharmacological therapies [19]. However, there are still limitations with current research, including small sample sizes and lack of detailed assessment of improvement and side effects [20]. In addition, the role of genetic polymorphisms in the treatment of IBS with acupuncture has not yet been studied. In 2014, our team conducted a meta analysis of IBS research in seven countries, and showed that there was a correlation between the 5-HTTLPR gene polymorphism and the incidence of IBS-D and IBS-C [21, 22]. As a result, large-scale, methodologically rigorous studies are needed to assess the effectiveness and safety of acupuncture for IBS as well as investigate the role of genetics in IBS.

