**Fig. 3 Fig3:**
[figure not shown]
Locations of acupoints: acupuncture group

The patients in the control group will receive standard pharmacological treatment based on the IBS subtype. Patients with IBS-C will take macrogol 4000 powders (Fu Song, two bags per day, dissolved in a glass of water before taking) for 6 weeks. Patients with IBS-D will take pinaverium bromide tablets (Dicetel, 50 mg tid, swallowing pills with water during meals without breaking, chewing or dissolving) for 6 weeks.

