### Outcome assessment

The primary outcome measure of this trial is the IBS-Symptom Severity Score (IBS-SSS), a validated scoring system for assessing the severity of IBS [24, 25]. The questionnaire is scored from 0 to 500 and is composed of five 100-point scales that measure the severity of pain, duration of pain, severity of abdominal distention, dissatisfaction with bowel habits, and disruption in life quality. The scores are classified into no IBS (< 75), mild IBS case (75–175), moderate IBS case (175–300), and severe IBS case (> 300) [25]. IBS-SSS is assessed at baseline, 1, 2, 4, 6, and 18 weeks.

The secondary outcome measures include the IBS-Quality of Life (IBS-QoL) and genotyping of the patients’ serotonin-related genes. The IBS-QoL is a 34-item questionnaire for determining the degree to which IBS interferes with the patient’s quality of life [26]. It is composed of eight dimensions, including dysphoria, interference with activity, body image, health worry, food avoidance, social reaction, sex, and relationships. Each item is evaluated on a 5-point rank scale with a higher score indicating a better quality of life. The IBS-QoL will be measured at baseline and 6 and 18 weeks.

DNA isolation and genotyping will be performed to study the possible correlation between the therapeutic effectiveness of acupuncture and the following polymorphisms of serotonin-related genes: (1) *HTTLPR* (*L/L*, *L/S*, *S/S*), (2) *STin2 VNTR* (*STin2 12/12*, *STin2 12/10*, *STin2 12/9*, *STin2 10/10*, *STin2 9/9*), and (3) *rs25531* (*rs25531-G*). The patients’ blood samples will be collected at the baseline. The correlation between IBS-gene subtypes and acupuncture effect will be detected based on cleaved amplification polymorphism sequence-tagged sites.

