Statistical analysis of all data in this study will be performed by a specialized statistician, who is blinded to the treatment allocation. Statistical Package for the Social Sciences (SPSS) V.24.0 (SPSS Inc., Chicago, IL, USA) will be used for data analysis. All analysis will be on the basis of the intention-to-treat (ITT) population and the per-protocol (PP) population. ITT requires all participants in a clinical trial to be included in the analysis in the groups to which they were randomized, regardless of any departures from randomized treatment. The PP population is usually defined as all patients completing the study without major protocol deviations – that is those who followed the rules of the study. The results of each population will be compared for stabilization. Last-observation-carried-forward will be used in the case of missing data. The principal investigator will take responsibility for the results of the data analysis. In terms of data description, quantitative and qualitative data will be presented as mean ± standard deviation, frequency, percentages or constituent ratios, respectively. Other covariates such as age, gender, ethnicity, disease duration, marital status, educational level, weight (in kilograms), and height (in meters) will be considered for further revision. In case of normality of distribution and homoscedasticity, the baseline characteristics will be performed using the analysis of covariance (ANCOVA) model, and the multiple comparisons will be performed with the Least Significant Difference test. In addition, a repeated- measure analysis of variance (rm-ANOVA) will be used to determine, within each group, the difference between baseline and 1, 2, 4, 6, and 18 weeks for both the IBS-SSS and the IBS-QoL. On this occasion of non-normal distribution data and heteroscedasticity data, the non-parametric Kruskal-Wallis test will be performed, and the Nemenyi test will be done to identify the difference between the groups. Pearson’s chi-squared test will be used in the transformed categorical data. Lastly, we will conduct rm-ANOVA to analyze genotype-related effects on treatment response. The Huynh-Feldt correction will be used if the assumption of sphericity is violated. A two-sided *p* value of less than 0.05 will be considered statistically significant for all analyses.

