The pathogenesis of IBS is still unclear, but a dysregulation of the brain-gut axis is thought to play a critical role in the disturbance of gastrointestinal function. Found in both the central nervous system and the gastrointestinal tract, serotonin is a major neurotransmitter involved in the brain-gut interaction. Elevated or reduced levels of serotonin have been implicated with diarrhea-predominant or constipation-predominant IBS, respectively [9]. The serotonin reuptake transporter (*SERT*) gene is responsible for regulating the intensity and duration of serotonergic signaling. Recent studies have shown that polymorphisms in the *SERT* gene are involved in the pathogenesis of IBS. For example, the prevalence of *5-HTTLPR l/l* and *rs25531 A/G* genotypes were found to be higher for patients with IBS compared to healthy controls [12]. Thus, there is increasing evidence for the role of genetics in the pathogenesis of IBS and growing interest in individualized treatments based on genetics studies [13]. Moreover, genetic variability may explain heterogeneity in treatment outcomes among different individuals. The effect of acupuncture on IBS symptoms may also be associated with the patients’ polymorphisms in the *SERT*-related genes. Therefore, this study will conduct genotyping of each patient to investigate the correlation between the polymorphisms of the *SERT* genes and therapeutic effect size.

From a TCM perspective, the brain-gut axis represents the interaction between the *Shen* (mind) and the Spleen. The Spleen is responsible for digesting food and generating energy for the whole body. Common manifestations of Spleen deficiency include abdominal pain, loose stools or constipation, and fatigue. Spleen deficiency is the most common syndrome associated with the diagnosis of IBS. Another important treatment principle for IBS is regulating the *Shen*. A disturbance in *Shen* or mental/emotional problems can also cause a problem in the Spleen. The close relationship between the Spleen and *Shen* is also demonstrated by studies showing the high prevalence of depression and anxiety among IBS patients compared to the healthy population. Therefore, it is important to address both the Spleen and *Shen* in treating IBS. The acupuncture points in this trial are selected in accordance with the TCM treatment principles of invigorating the Spleen and regulating the *Shen*.

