Nevertheless, there are still limitations in this study that should be noted. First, the main outcome measures are subjective evaluation scales which lack objective evidence to support the effect of a given treatment directly. Second, after completion of the 6-week treatment, a 3-month follow-up will be conducted, the drop-out rate may be higher. In order to minimize potential drop out, we have established guidelines and training for research staff to establish good communication relationships with the participants.

In conclusion, the results of this methodologically rigorous trial are expected to not only provide clinical evidence of the effectiveness and safety of acupuncture in treating IBS, but also investigate the role of genetics in IBS.

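### The planned genotype analysis does not name IBS subtype, so a subtype or control-drug difference in response could pass as a genotype effect if genotype shares differ between IBS-C and IBS-D

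*Protocol article*

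**What the plan says.** - **Objective.** Under Outcome assessment, genotyping is a secondary measure, meant to "study the possible correlation between the therapeutic effectiveness of acupuncture and the following polymorphisms of serotonin-related genes". Three polymorphisms are listed: HTTLPR, STin2 VNTR and rs25531.
- **Analysis.** Under Sample size calculation and statistical analysis: "Lastly, we will conduct rm-ANOVA to analyze genotype-related effects on treatment response". The factors of that model are not listed. The same section names eight example covariates (age, gender, ethnicity, disease duration, marital status, education, weight, height). Subtype is not among them.
- **Subtype in the design.** Study design and Randomization and blinding make IBS-C or IBS-D the randomization stratum.
- **Subtype and treatment.** Under Acupuncture and the control group, acupuncture is the same in both subtypes, but the control drug differs. IBS-C controls take macrogol 4000, while "Patients with IBS-D will take pinaverium bromide tablets".
- **Subtype and genotype.** The Background reports the team's own meta-analysis, which "showed that there was a correlation between the 5-HTTLPR gene polymorphism and the incidence of IBS-D and IBS-C". The Discussion adds: "Elevated or reduced levels of serotonin have been implicated with diarrhea-predominant or constipation-predominant IBS, respectively", and says that the SERT gene regulates serotonin signalling.
- **Scope wording.** The article's closing paragraph says that the trial will provide evidence on acupuncture, "but also investigate the role of genetics in IBS". The abstract's Discussion says: "This is the first time ever that the potential mechanism of IBS based on genomics has been investigated". Every participant has IBS-C or IBS-D.

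**The concern.** Randomization within subtype balances the arms. It does not balance genotype against subtype. If one genotype is commoner in IBS-D than in IBS-C, genotype partly stands for subtype, and two things can follow.

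1. **Within the acupuncture arm.** Treatment is identical, so the drug plays no part. If IBS-C and IBS-D respond differently to acupuncture, part of that difference appears as a genotype difference.
2. **In a genotype-by-arm contrast.** Subtype also fixes the comparator, so each genotype group is compared with a different mix of macrogol and pinaverium. A difference in effect between the two drugs can then appear as a genotype-by-treatment interaction. Testing the interaction does not remove this unless subtype-by-treatment is also in the model.

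At stake is whether a genotype is reported as a marker of acupuncture response when it only marks subtype or comparator.

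**Working it through.** **The plan's own figure.** The only stated calculation is for the primary comparison: difference 115 − 105 = 10 points, SD 37, 2:1 allocation, 80% power, two-sided 5%. Control n = (1 + 1/2) × (1.960 + 0.842)² × (37/10)² ≈ 161.2, rounded up to 162, with 324 for acupuncture. The article states 161 and 322, so its figure reproduces to within rounding. It states none for the genotype analysis. What follows therefore borrows SD 37 and 400:200 from the document, and everything else is assumed.

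**Assumptions.** Genotype in two groups, subtypes 50:50, overall genotype share 50%, no true genotype effect, one change score per patient with SD 37, no losses.

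**Bias formula.** Spurious contrast = (IBS-D share among carriers − IBS-D share among non-carriers) × (gap between subtypes). The gap is in acupuncture response for the single-arm analysis, and in the acupuncture-minus-drug effect for the genotype-by-arm contrast.

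Example: the genotype is carried by 40% of IBS-C and 60% of IBS-D.
- IBS-D share among carriers: 0.5×0.6 / (0.5×0.6 + 0.5×0.4) = 0.6. Among non-carriers: 0.4. Difference 0.2.
- With a gap of 20 points (20/37 = 0.54 SD), bias = 0.2 × 20 = 4 points.
- Acupuncture arm: SE = 37 × √(1/200 + 1/200) = 3.70. Bias/SE = 1.08, so a two-sided 5% test rejects in 19.1% of trials.
- Genotype-by-arm: SE = 37 × √(1/200 + 1/200 + 1/100 + 1/100) = 6.41. Bias/SE = 0.62, so it rejects in 9.6%.

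**False-positive rates.** The first two rate columns are normal approximations. The last two are simulations of the genotype-by-arm test, 2,000 runs each.

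| Genotype share, IBS-C / IBS-D | Gap (points) | Bias (points) | Acupuncture arm, no subtype term | Genotype-by-arm, no subtype term | Simulated, no subtype term | Simulated, with subtype and subtype-by-treatment |
|---|---|---|---|---|---|---|
| 50% / 50% | 20 | 0 | 5.0% | 5.0% | 5.0% | 5.0% |
| 45% / 55% | 10 | 1 | 5.8% | 5.3% | not run | not run |
| 40% / 60% | 10 | 2 | 8.4% | 6.1% | 6.8% | 5.6% |
| 40% / 60% | 20 | 4 | 19.1% | 9.6% | 10.8% | 5.1% |
| 35% / 65% | 20 | 6 | 36.8% | 15.5% | 15.1% | 4.4% |

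The simulation standard error at 5% is √(0.05 × 0.95 / 2000) ≈ 0.5 percentage points, so 4.4% to 5.6% is consistent with 5%. The adjusted model was simulated only for the genotype-by-arm test. In the acupuncture arm the same remedy follows by argument: with subtype in the model, carriers and non-carriers are compared within subtype, where the assumed genotype effect is zero.

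**Price of adjustment.** In this set-up the genotype-subtype correlation equals the difference in shares. Adjustment multiplies the variance of the genotype estimate by 1/(1 − r²): 1/(1 − 0.04) = 1.04 at 40%/60%, and 1/(1 − 0.09) = 1.10 at 35%/65%.

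**The case against.** The other side has a good deal of substance.

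- **Pooling is not stated.** A reader might infer that the trial pools the subtypes in the genotype analysis. The article does not say so. It lists no factors at all, the covariate list is open-ended, and a fuller model may sit in an analysis plan that is not shown. This stands. What remains is that the text names eight covariates and leaves out the stratification factor, although its own background gives a reason to include it.
- **Unequal shares are not stated.** A reader might take the Background as saying that genotype shares differ between IBS-C and IBS-D. It reports "there was a correlation between the 5-HTTLPR gene polymorphism and the incidence of IBS-D and IBS-C", with no size, no direction and no comparison of the two. If the association is the same in both, the shares match and the bias is zero. The opposite serotonin levels described in the Discussion make a difference plausible, but they are not genotype frequencies.
- **One polymorphism, not three.** The stated link covers 5-HTTLPR. Nothing in the article ties STin2 or rs25531 to subtype.
- **The drug enters only with the control arm.** The stated objective concerns the effect of acupuncture. An analysis confined to that arm is open to confounding by subtype, not by drug.
- **The magnitudes are assumed.** Larger assumptions could bring the bias near the trial's 10-point target. That target is a difference between arms, a different quantity, and the likeness would come from the inputs chosen.
- **The role of genetics in IBS.** A reader might conclude that the design fails because there is no non-IBS group. The working aims are narrower and concern genotype and response. No case-control analysis is planned, so none is invalid. The broad sentences are a matter of wording.

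**Conclusion.** The point holds in conditional form. As written, the genotype analysis names no subtype term, so it is open to confounding by subtype in the acupuncture arm and by subtype and control drug in any contrast with control. The documents do not show that this bias will occur, because they give neither genotype shares nor responses by subtype.

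Under the assumptions above, the false-positive rate runs from 5% (equal shares) to 6.8–15.1% in the simulated genotype-by-arm settings with unequal shares. In the acupuncture arm at 40%/60% it is 8.4% with a 10-point gap and 19.1% with a 20-point gap. Subtype and subtype-by-treatment terms brought the simulated test back to about 5%.

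This concerns a secondary analysis and leaves the primary comparison untouched. It is still worth settling before analysis, because the cure is specific and almost free. The scope wording is a minor point that changes no analysis.

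**What to change.** 1. State that the genotype model includes IBS subtype, with subtype-by-treatment where the control arm is used. Equivalently, estimate the genotype effect within IBS-C and within IBS-D and combine the two.
2. State that any conclusion about genotype and acupuncture response rests on that within-subtype estimate.
3. As a minor edit, limit the sentences on the role of genetics or the mechanism of IBS (abstract Discussion, end of Background, closing paragraph of the Discussion) to genotype and treatment response among patients with IBS. No new objective on genotype frequencies is needed.

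The cost is a few lines of text. Subtype is known at randomization and blood is drawn at baseline, so no data need be added, and Trial status describes the trial as still ongoing. The downside is slightly less precision, felt mostly for rare genotypes, which become thinner once split by subtype.

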## Abstract

**Background:**

Irritable bowel syndrome (IBS) is a chronic gastrointestinal disorder characterized by abdominal pain and change of bowel habit without organic disease. A global perspective given by the World Gastroenterology Organization (WGO) points out that IBS can impact the quality of an individual’s daily life, cause socioeconomic problems and potentially impair the patient-physician relationship. It remains a problem to treat IBS due to the complicated pathophysiology. Acupuncture is an alternative therapy recommended for IBS. The aim of this study is to investigate the efficacy and safety of acupuncture therapy for patients with IBS. We also want to explore the correlation between IBS-gene subtypes and acupuncture effect.

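### The genotype analysis names no genotype-by-treatment term and sets an unadjusted 0.05 over three loci, so as written it does not separate prognostic genotypes from those that modify the acupuncture effect

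*Protocol article*

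**What the plan says.** **Aim.** The Abstract (Background) puts it as "We also want to explore the correlation between IBS-gene subtypes and acupuncture effect". Outcome assessment says genotyping is done to study "the possible correlation between the therapeutic effectiveness of acupuncture and the following polymorphisms of serotonin-related genes", and names three loci: HTTLPR, the STin2 VNTR and rs25531. It lists genotyping with the secondary outcome measures, although the blood is to be taken at baseline. The Discussion says "this study will conduct genotyping of each patient to investigate the correlation between the polymorphisms" of the SERT genes and the size of the therapeutic effect.

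**Analysis.** Sample size calculation and statistical analysis gives one sentence: "we will conduct rm-ANOVA to analyze genotype-related effects on treatment response". It does not say which arms enter the model or which terms are tested. The other repeated-measures ANOVA in that section "will be used to determine, within each group, the difference between baseline and 1, 2, 4, 6, and 18 weeks".

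**Threshold.** A two-sided p "value of less than 0.05 will be considered statistically significant for all analyses". For normally distributed data, the only multiple-comparison procedure named is in the sentence on baseline characteristics and ANCOVA: "the multiple comparisons will be performed with the Least Significant Difference test".

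**The concern.** The aim is about the acupuncture effect, which in a randomised trial is a difference between arms. The named analysis is about response, which is what happens to a patient on treatment. Carriers of a genotype may improve more whatever they receive, through a milder course, stronger regression to the mean or a larger non-specific response. Such a genotype is prognostic. It would be associated with response among acupuncture patients, and in the pooled sample, without altering the benefit of acupuncture over the drug control. Only the contrast of treatment effects between genotype groups, using the randomised controls, tells the two apart.

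At stake is a named secondary aim: a general prognostic marker could be reported as predicting benefit from acupuncture. The unadjusted threshold over three loci adds some risk of a chance finding. The primary treatment comparison is not affected.

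**Working it through.** **Inputs from the document** (Sample size calculation and statistical analysis): improvement on the IBS-SSS of 115 points with acupuncture and 105 with control, so a difference of 10; SD 37; ratio 2:1; 80% power; 5% type I error; 322 and 161 required; 400 and 200 enrolled. Outcome assessment gives three loci.

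**Assumptions (not in the document):** a two-level genotype (carrier or not) with carrier share q of 0.1, 0.3 or 0.5; improvement at a single time point with SD 37; 322 and 161 patients analysed; two-sided tests.

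**1. The plan's own sample size.** Control n = (1 + 1/2) × (1.960 + 0.842)² × 37² / 10² = 161.2. Rounded up this is 162 and 324; the stated 161 and 322 have 79.8% to 80.0% power. The figure reproduces. The document gives none for the genotype analysis.

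**2. A purely prognostic genotype.** Let carriers improve by 10 points more in both arms, with no effect modification. The standard error of a carrier contrast in n patients is 37 × √[1 / (n q(1−q))]. Power is about Φ(10/SE − 1.96).

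| Test | q = 0.5 | q = 0.3 | q = 0.1 |
|---|---|---|---|
| Acupuncture arm only, n = 322 | SE 4.12, 68% | SE 4.50, 60% | SE 6.87, 31% |
| Both arms, genotype main effect, n = 483 | SE 3.37, 84% | SE 3.67, 78% | SE 5.61, 43% |

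A simulation with 4,000 runs gave 66% and 84% at q = 0.5, and 60% and 78% at q = 0.3. In the same runs the genotype-by-treatment test rejected in 4.8% (q = 0.5) and 5.9% (q = 0.3), close to its nominal 5%. So a significant genotype effect on response does not by itself point to the acupuncture effect.

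**3. Multiplicity over loci.** One test per locus at 0.05, taken as independent: 1 − 0.95³ = 0.143. Positive correlation between the tests would lower this. Holm would begin at 0.05/3 = 0.0167.

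**4. Power of the interaction test.** SE = 37 × √[(1/322 + 1/161) / (q(1−q))]. The difference in treatment effect is set to 10 points, the size of the whole planned treatment difference.

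| q | SE | Power, α = 0.05 | Power, α = 0.0167 | Difference detectable with 80% power, α = 0.05 |
|---|---|---|---|---|
| 0.5 | 7.14 | 29% | 16% | 20 points |
| 0.3 | 7.79 | 25% | 13% | 22 points |
| 0.1 | 11.90 | 13% | 6% | 33 points |

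The main treatment comparison has SE 37 × √(1/322 + 1/161) = 3.57, so the interaction SE is at least twice as large.

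**5. Genotype list.** Alleles 9, 10 and 12 give 3 × 4 / 2 = 6 STin2 genotypes. Outcome assessment lists five; 10/9 is absent.

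**The case against.** The strongest reply is that the sentence is silent on model terms rather than wrong. It does not exclude a genotype-by-arm term, the within-group restriction belongs to a different sentence, and a condensed article may leave model terms to a fuller document. A reader might infer that the planned analysis cannot show a link with the acupuncture effect; the text does not support that. What stands is that the article does name a target for this analysis, genotype effects on response, and this is not the quantity in the aim.

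Second, the aim is worded as exploratory, and many statisticians do not adjust exploratory tests. That lessens the multiplicity point. It does not remove it, because genotyping is listed with the secondary outcomes and the section applies one significance threshold to all analyses without exempting this one.

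Third, a reader might conclude that a spurious gene finding is likely, by multiplying the three loci by two IBS subtypes or two scales. The document does not say that the genotype tests are split in these ways, so only the 14% follows from the text, and that under independence. Nor is the least significant difference test said to apply to the genotype analysis.

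Fourth, a reader might infer that STin2 10/9 carriers would be dropped. The list names polymorphisms, not analysis classes, and no frequency is given. It is a small listing gap of unknown effect.

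Finally, the interaction test has low power. That is correct and has to be reported, but it is no reason to rely on a test of a different question.

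**Conclusion.** The point holds in a limited form. As written, the genotype analysis does not distinguish genotypes that predict improvement on any treatment from genotypes that modify the acupuncture effect, and it carries an unadjusted 0.05 over three loci.

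The gap matters if a prognostic genotype exists. With an assumed 10-point prognostic effect, a genotype test on response would be significant in roughly 60% to 84% of trials at carrier shares of 0.3 to 0.5 (31% to 43% at 0.1), with no effect modification present. The familywise error is about 14% for three independent tests. Genotype shares and the 10-point prognostic effect are assumptions. The sample size for the treatment comparison is not in error on this account.

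The point deserves a change because the Discussion commits to genotyping every patient, so the control data needed for the right contrast will exist.

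**What to change.** - Analyse both randomised arms together, with genotype, treatment and time, adjusted for baseline score and IBS subtype. Name genotype-by-treatment (by time) as the test.
- Describe a genotype as related to the acupuncture effect only on the basis of that interaction estimate with its confidence interval, and report it as relative to the drug control, which differs between IBS-C and IBS-D.
- Either adjust across the three loci (for example Holm) or label the genotype analysis explicitly as exploratory and exempt it from the general significance rule.
- Treat genotype as a baseline factor, not an outcome, with a coding (for example per allele or by carrier status) that also places STin2 10/9 carriers.
- State that interaction power is low, with the assumed genotype shares, so that a null result is read as inconclusive.

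**Cost.** Only the analysis text changes. Trial status reports 540 of the planned 600 participants recruited and the trial ongoing; no new data are needed beyond the baseline blood samples and genotyping already planned. The price is lower power than a test on response, and lower still with adjustment: 6% to 16% at 0.0167, against 13% to 29% at 0.05, for a 10-point difference in treatment effect.
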